### Setting and clusters

The setting is primary care in England for adults with musculoskeletal problems (GP practices and linked NHS physiotherapy services). GP practices are the unit of randomisation, and thus, patients follow the care pathways to which the practice is randomised. In this pilot, RCT practices will be stratified only on practice size, but in a main trial, practices would also ideally be stratified by index of deprivation. Randomisation of GP practices will be undertaken by an independent statistician. GP practices will be randomised to one of two arms, either to continue with usual GP-led primary care for musculoskeletal patients with the addition of the offer of a self-referral physiotherapy pathway (intervention group) or to continue with usual GP-led primary care alone (usual care control group). Practices will be randomised according to a computer-generated random numbers stratified by the practice size (small or large) in the ratio 1:1. In a main study, we would plan to further stratify by practice setting and area level deprivation (through minimisation) in order to ensure balance in key practice characteristics in each arm of the trial.

GP practices are eligible to take part if they meet the following criteria: they are within the Vale Royal Clinical Commissioning Group area of Cheshire and the Clinical Research Network (CRN); they are a group practice, currently referring musculoskeletal patients to NHS physiotherapy services; they do not currently offer direct access to physiotherapy; and they are willing to test direct access. The balance between scientific considerations and the need for consent is a known issue for cluster trials [27]. Informed consent for practices to participate will be provided by the senior GP partner in each practice acting as ‘guardian’ for patients in their care. Patients will follow the care to which their practice is randomised with identical patient information for both arms providing general information about the study, explaining that their local musculoskeletal services are being evaluated using patient self-reported clinical outcomes and medical record review. Individual patients will therefore be able to opt out of data collection.

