### Participant identification and recruitment

Following randomisation of GP practices, potentially eligible participants will be identified through one of three methods.

Method 1: Patients consulting GP practices with a musculoskeletal problem will have a musculoskeletal Read code^1^ (entered by GPs or nurse practitioners) entered into their computerised medical record. A member of the GP practice team, or CRN staff, will download the details of patients with these Read codes twice weekly checking for exclusion criteria and then forward these details to a CRN administrator. GPs will be able to exclude any patients they perceive as being particularly vulnerable and unsuitable to approach for involvement in research by using a dedicated exclusion code set up for the study.

Method 2: In addition, for those GP practices randomised to also offer direct access to physiotherapy, patients who self-refer to physiotherapy will be identified when they forward a completed self-referral form to the physiotherapy service or telephone the physiotherapy administrator for help in completing a form. As in method 1 the details of identified patients will be forwarded to a CRN administrator.

Method 3: Patients referred by GPs or practice nurses to the physiotherapy service, but not identified in method 1 due to an absence of an appropriate Read code in the computerised medical records, will be identified from the physiotherapy administration database. A physiotherapy administrator will download the details of all patients referred from the participating GP practices twice weekly and forward these details to a CRN administrator. Duplication checks will ensure that eligible patients are not invited to take part in the research more than once.

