### Methods for protecting against sources of bias

Allocation concealment for participating GPs and physiotherapists is not possible, and therefore, to prevent recruitment bias, neither of these groups of clinicians will be involved in recruiting participants into the research evaluation. Instead eligible participants will be identified from electronic GP medical records and from the physiotherapy service database, conducted by CRN staff. We will follow the CONSORT guidelines for both cluster trials and non-inferiority trials [28, 29]. In an ideal world, the comparison would be all patients who have a musculoskeletal problem in the participating practices during the study period, whether or not they attend their GP and/or physiotherapy service, but clearly this is not possible. Therefore, all patients who consult their GP practice (control arm) will be compared with all patients who consult their GP or physiotherapy service (intervention arm) with a musculoskeletal condition. Patients who directly access physiotherapy may be different in important ways to those who consult their GP, which is a limitation of the design. Therefore, in the pilot trial, we will investigate whether the number of consulters (to GPs only in the control arm and to either GPs or physiotherapists in the intervention arm) that have been identified in each arm are similar, whether there appears to be any differential uptake to the research evaluation in the two arms and whether the baseline characteristics of participants in each arm are similar.

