### Outcome measures

Process outcomes: Process outcomes will determine if a future main trial is possible and desirable. Anonymised process outcome data will be collected from GP records and physiotherapy administration databases and self-referral forms. Health service process outcomes include the proportion of patients not referred to physiotherapy services, those referred to physiotherapy and the number of patients directly accessing physiotherapy in the intervention practices, proportion of ‘recommended self-referral’ and ‘true self-referral’ in the direct access pathway, waiting times for treatment (time from logging of referral to first physiotherapy appointment), number of GP and NHS physiotherapy consultations for musculoskeletal problems and non-attended physiotherapy appointments (DNA rates). Research process outcomes include estimation of recruitment rates, exploration of evidence of selection bias and follow-up rates at each time-point with differences in the control and intervention practices explored to identify sources of bias. A summary of the process measures is shown in Table 1.

**Table 1 Tab1:** STEMS pilot trial process measures

Engagement of GP practices and PT services
Physiotherapy site recruitment rate to participate in STEMS study
GP Practice recruitment rate to participate in STEMS study
Research evaluation
Recruitment rate to the research evaluation—all adults with musculoskeletal conditions
Recruitment rate to the research evaluation—‘true self-referral’^a^ patients
Recruitment rate to the research evaluation—‘recommended self-referral’^b^ patients
Retention rates to research evaluation at 2, 6 and 12 months follow-up
GP practice characteristics
Number of GPs and nurse practitioners per practice
Number of patients and number of adults registered at practice
GP consultation rates for adults with musculoskeletal conditions (before and during study)
Physiotherapy team characteristics
Number of physiotherapists working in the physiotherapy service (in total and STEMS trained)
Seniority of physiotherapists in the physiotherapy service (in total and STEMS trained)
Physiotherapy service
Physiotherapy service GP referral rate (before and during study)
Physiotherapy service ‘true self-referral’^a^ rate
Physiotherapy service ‘recommended self-referral’^b^ rate
Non-attendance rates at physiotherapy site for GP referrals (before and during study) and for self-referrals during study

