#### Evidence of selection bias

Since this is a pilot trial with only four clusters randomised, it is likely that there will be some imbalance between participants in each of the treatment arms on one or more baseline characteristics. Baseline comparisons will be carried out to detect any substantial differences between participants recruited from the control and intervention arms. This will be done by scrutinising the baseline table for any serious imbalances in observable baseline variables and the trends of the imbalance if any. The recruitment rates will also be estimated and compared between the control and intervention arms. We will examine the size of any imbalances and decide if there is evidence of systematic selection bias in the types of patients being recruited in control versus intervention arms. Any systematic imbalance in the sense that one arm is consistently favoured by the imbalances may not reflect chance alone and may suggest selection bias.

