### Design considerations and limitations

We acknowledge that a limitation of the trial design is recruiting patients in the control arm from GP practices and in the intervention arm from GP practices and the physiotherapy service. In an ideal design, we would compare all patients who have a musculoskeletal problem registered with participating practices during the study period, whether or not they attend their GP and/or physiotherapy service but clearly this is not possible. Other trial designs were considered, but these would have led to greater differences in patients recruited to the two arms of the trial. We will therefore make considerable efforts to identify any evidence of selection and recruitment bias between the arms of the pilot trial, although we acknowledge that patients may differ on other unknown factors.

It is possible that over time, as patients become accustomed to direct access, their expectations and service use may change. Clinical outcomes are unlikely to change beyond 12-month follow-ups, but costs and benefits may change as direct access becomes established within a community. Therefore, this pilot trial includes follow-up to 12 months as longer follow-up would be expensive within the context of a trial.

This pilot aims to inform a main trial with a non-inferiority design as the addition of a direct access to physiotherapy pathway is not anticipated to be superior in terms of patients’ clinical outcomes. However, a range of secondary outcomes is included that in a main trial will provide important information for patients, health care practitioners and commissioners if clinical non-inferiority is demonstrated. Previous work suggests an effect size of 0.2 to 0.6 as a minimum clinically important difference, and we would thus, anticipate specifying a difference between groups of 0.2 as the threshold for the purposes of demonstrating non-inferiority in a main trial.

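### The check for extra patients in the intervention arm compares raw numbers of consulters, which a 5–6% difference in practice list size could mimic or hide

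*Protocol article*

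**What the plan says.** The section on protecting against bias states the limitation plainly: "Patients who directly access physiotherapy may be different in important ways to those who consult their GP, which is a limitation of the design". The section on design considerations repeats it as "recruiting patients in the control arm from GP practices and in the intervention arm from GP practices and the physiotherapy service". In response, the pilot will investigate "whether the number of consulters (to GPs only in the control arm and to either GPs or physiotherapists in the intervention arm") is similar. The same sentence adds two further checks, on uptake and on comparability at baseline: "whether there appears to be any differential uptake to the research evaluation in the two arms and whether the baseline characteristics of participants in each" (the quote stops just short of the sentence's end).

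Practice size is handled at randomisation, which is "stratified by the practice size (small or large) in the ratio 1:1". The selection-bias part of the analysis begins "Since this is a pilot trial with only four clusters randomised" and relies on the baseline table and recruitment rates. It mentions neither a consulter count nor a consulter rate.

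The data for a rate are planned elsewhere. Table 1 lists "Number of patients and number of adults registered at practice", together with GP musculoskeletal consultation rates before and during the study. The analysis presents these under practice engagement, not under selection bias.

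**The concern.** The number of consulters identified in an arm is the product of how many people are registered and how often they consult. Only the second factor bears on the question, which is whether direct access draws in people who would not otherwise have consulted. A raw count mixes the two. If the intervention practices have larger lists, equal consulting behaviour looks like an influx. If they have smaller lists, a real influx can disappear.

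The pilot is meant to show whether the two arms of a main trial would be comparable. A misleading answer here would carry forward into the main trial's recruitment design.

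**Working it through.** **Inputs from the protocol article**
- Sample size: 100 consulters per month from a 5,000-patient practice, 80% eligible, 50% recruited, four practices, 6 months.
- Description of control arm: about 20–25% of consulters referred on. The sentence also mentions tests and other services; here the whole share is taken as physiotherapy.
- Feasibility of direct access: at least 20% of the intervention-arm physiotherapy caseload to come through direct access.

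**Step 1: reproduce the plan's figures.** 100 × 0.80 × 0.50 × 4 × 6 = 960 at baseline, and 0.80 × 960 = 768 followed up. Both match. The monthly 100 is rounded down from 1,250/12 = 104.2; the rounded figure is used below.

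**Step 2: consulters expected per arm.** Two practices per arm gives 2 × 100 × 6 = 1,200 on 10,000 registered patients, or 0.12 per registered patient over 6 months.

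**Step 3: size of influx at the direct-access target.** GP referrals are 0.20 × 1,200 = 240 to 0.25 × 1,200 = 300. If direct access adds to these and makes up 20% of the total, the number is GP referrals × 0.20/0.80, which is 60 to 75. If every one were extra, the arm's count would rise by 60/1,200 = 5.0% to 75/1,200 = 6.25%.

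The target is a floor. The Background cites a 22–28% self-referral share from the Netherlands. At 28% with 300 GP referrals, the same formula gives 300 × 0.28/0.72 ≈ 117, or 9.7%.

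**Step 4: list-size difference with the same effect.** 5.0–6.25% of 10,000 is 500–625 registered patients per arm.
- Mimicked: control list 10,000, intervention list 10,625, no extra patients. Counts are 1,200 and 1,275, a ratio of 1.0625.
- Hidden: control list 10,625, intervention list 10,000, with 6.25% extra. Counts are 10,625 × 0.12 = 1,275 and 10,000 × 0.12 × 1.0625 = 1,275, which are identical. Per registered patient the ratio is (1,275/10,000)/(1,275/10,625) = 1.0625, so the rate recovers the influx.

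**Step 5: precision of the rate.** With 1,200 per arm, the Poisson standard error of the log rate ratio is √(2/1,200) = 0.041, and 1.96 × 0.041 is about 8%. Between-practice variation with coefficient of variation c and two practices per arm gives √(2/1,200 + 2c²/2). The half-width on the log scale is then about 13% for c = 5% and 21% for c = 10%. These two values of c are illustrative; the article gives none.

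**Step 6: what the other planned items measure**
- Uptake is conditional on having been identified, so it cannot show that the identified pool grew.
- Baseline similarity is an indirect signal. The article expects chance imbalance with four clusters and warns that many baseline questionnaires will follow the first consultation.
- Counts of self-referrals show use of the route. They do not show how many users would otherwise have seen the GP.
- The before/during rate covers GP consultations only. It falls if direct access substitutes for GP visits and stays level if it adds to them. It answers the question only when combined with the patients who bypassed the practice, and the article does not make that combination.

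**The case against.** A reader might infer that the pilot has no means of detecting an influx. The article does not support that. It reports participants by recruitment method, and the self-referral method exists only in intervention practices. It counts GP referrals, recommended self-referrals and true self-referrals separately, stratifies on practice size, and presents list sizes and GP rates. A careful analyst could assemble the rate from these. What is missing is the link between those data and this check. Nor is the count the only response to the limitation: uptake, baseline characteristics, characteristics by recruitment method and comparisons of self-referrers with others all address whether the patients differ in kind, which no count could settle.

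A reader might also infer that counting GP consulters only in the control arm drops the uncoded patients found on the physiotherapy database. That does not follow. The phrase says whom control patients consult, not which database finds them. The database search covers both arms ("A physiotherapy administrator will download the details of all patients referred from the participating GP practices twice weekly"), the patients it adds were referred by a GP or nurse, and duplicates are removed.

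Nor do the article's figures support an influx as large as 20% of an arm's consulters; Step 3 gives 5–6% at the target.

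It can fairly be said that this is one sentence in a condensed article and that detail belongs in the analysis plan. But the sentence names a quantity, the number of consulters, and that quantity is the wrong one. It is also true that a rate from four practices will be imprecise relative to a 5–6% effect. That limits what the check can conclude. It is no reason to keep a list-size distortion that is easily removed.

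**Conclusion.** The point stands in moderate form. As worded, the check compares a quantity that depends on list size. At the article's own direct-access target, a list difference of about 5–6% between arms could wholly mimic or hide the largest influx expected.

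The size rests on these assumptions: equal 5,000-patient lists as the starting point; the 20–25% referral share taken as all physiotherapy; direct-access patients added to GP referrals; the target just met; and every direct-access patient extra. The last is an upper bound, because recommended self-referrers have already contacted their practice. A direct-access share above the target would raise the figure. The actual lists are not given, so whether an imbalance of this size will occur is unknown; a two-level stratum does not rule it out.

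Using a rate removes the distortion but does not make the check decisive. With four practices it remains a descriptive item to be read with the other planned comparisons.

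**What to change.** State the check as the number of patients identified as consulting for a musculoskeletal problem, by GP practice or physiotherapy and each counted once, per 1,000 registered adults, by practice and by arm. Show beside it each practice's own pre-study musculoskeletal consultation rate, in the same unit (patients, not visits), for a period that ends before marketing of direct access begins. Before launch these practices had no direct access, so the GP-based rate is a reasonable pre-study comparator. Show true self-referrals as a separate component. Report the ratio between arms with a confidence interval and treat it as descriptive.

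Before true self-referrals are used this way, the Table 1 footnotes need reconciling with the text: they define true and recommended self-referral the opposite way round from the intervention description, the direct-access analysis and the discussion.

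The cost is a few lines of wording in the analysis plan and one table. List sizes and GP rates before and during the study are already in Table 1, and self-referrals are already counted by type. The only new work is building the combined de-duplicated numerator and putting the pre-study rate in the same unit.

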Both primary and secondary outcomes are based on self-report postal questionnaires; therefore, no investigator bias will be introduced at assessment. The research nurses involved in helping patients to complete questionnaires and minimum data collection will be based in the Clinical Research Network, not in participating practices, and will be kept blind to practice allocation. Success of blinding will be recorded on the Minimum Data Collection form. In addition, the trial statistician undertaking the analysis will also be blind to practice allocation. Using validated outcome measures for self-report will guard against measurement error. Quality control including data entry, coding, security, storage and management will be performed according to the Standard Operating Procedures of the Keele Clinical Trials Unit. A random 10 % of the participants’ data entered will be compared with the paper versions to check data entry accuracy. Data accuracy will be audited and accuracy rates recorded. Loss to follow-up will be minimised by implementing standardised reminder procedures and minimal data collection for non-responders. Participants will be free to withdraw from the research at any time without having to give any explanation. Where possible, we will collect information about the reasons for withdrawal. All records will be kept confidential and data sets for each participant will be identified by the patient’s participant number. Analysis will be performed on an intention-to-treat (ITT) basis using the full set of available data (mixed model and multiple imputation of missing data). Patients self-referring or being GP-referred receive equitable treatment, for example, in the length of wait to first physiotherapy contact once they are logged on the physiotherapy administration system. The physiotherapists participating in the trial will provide physiotherapy care to patients from both arms of the trial (initiated from traditional GP referral in the control arm versus from both traditional GP referral and patient self-referral in the intervention arm). As this trial is investigating the addition of direct access to physiotherapy, the physiotherapy care provided will be determined by clinical need and assessment findings and will therefore be consistent with routine practice and not differ for patients in different arms of the trial.

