#### Explore generalisability of the sample

Anonymised data on key baseline characteristics (age, gender and index of multiple deprivation (from post-codes)) of those who are invited but who do not participate will be compared with those who do participate. Key baseline characteristics will be compared between those participants followed up and those lost to follow-up at each time-point. Key characteristics of the participants recruited using each recruitment method will be reported. Delays in return of questionnaires (>35 days from initial mailing date) will also be compared between the two arms.

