#### Analyses of clinical outcomes

Analyses will be conducted for the clinical outcomes, but this will be treated as exploratory and will be mainly descriptive. A baseline table (descriptive statistics and frequencies) will compare the demographic and clinical characteristics (gender, age, education, employment status, pain interference with performance at work, type of accommodation, health literacy, physical health (SF-36v2 PCS) and mental health (SF-36v2 MCS), pain location, physical function, pain duration, baseline risk of persistent problems, comorbidities, pain self-efficacy, understanding of the condition, experience of care and convenience and accessibility of service) between the two arms. Since the baseline assessment for the clinical characteristics will be completed, for many patients, after their initial consultation about their musculoskeletal problem, there could be implications on evaluation and interpretation of these measures as they may not be ‘true baseline’ but rather possible ‘outcomes’ at the first time-point. All continuous variables will be summarised using mean, standard deviation, median and interquartile range as appropriate. The frequency and percentages of observed levels will be reported for all categorical measures.

As this is a pilot trial, no emphasis will be put on the *p* values for any inferential statistical tests conducted. A mixed effect model, which allows all available data at all the four time-points to be used and account for missing data and clustering effect, will be used to estimate a two-sided 95 % CI to show a credible range for the true difference in the SF-36v2 PCS subscale between intervention and the control arms. The model will be adjusted for key patient-level baseline characteristics (age, area level deprivation and widespread pain (from manikin data)) and a random effect for the GP practices and will include a treatment-by-time interaction to obtain the estimates of treatment effect (and 95% CI) at each follow-up visit (2, 6 and 12 months). Analyses of the secondary outcomes will be performed similarly.

Further analysis will descriptively compare the baseline characteristics and key clinical outcomes between the participants referred to physiotherapy in the control practices with participants self-referring in the intervention practices. We will also compare the self-referrers with those that do not self-refer within the intervention group.

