### Data confidentiality and archiving

The transportation of electronic sensitive data originating from NHS sources, such as contact details or medical records, will be conducted in accordance with the guidelines provided by NHS National Information Governance Board (NIGB). Data collected as part of the medical record review of consenting participants will be recorded on NHS compatible encrypted laptop computers and then transferred to university computers. Any transfer of personal information between CRN staff and GP practice or physiotherapy service administrators will be transferred using NHS email accounts. Paper records kept for research purposes will include hard copies of the completed questionnaires with signed consent forms and case report forms (CRFs). Consent forms will contain names and address but will be stored in a secure environment separate from patient data. The contact details of consenting participants will be required for mailing the follow-up questionnaires for this study. These contact details will be stored on a separate database to their questionnaire responses and clinical data, linked by their unique ID number. All trial-related information will be stored securely at the Research Institute for Primary Care and Health Sciences at Keele University. Coded identification numbers will be used to anonymise data with the data and the linking code stored in separate locations, under password protection. Access to the data will be to the small number of individuals necessary for quality control, audit and analysis. The final trial dataset will be accessed by the statistician (RO), the trial principal investigator (AB) and chief investigator (NEF). We will publish and communicate the pilot trial results regardless of the outcome of the trial. Data from the STEMS pilot trial will be archived and made available for future, secondary analysis and data pooling purposes from the Research Institute for Primary Care and Health Sciences at Keele University.

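### The statement that the analysing statistician is blind to practice allocation cannot hold for the whole analysis described and should be limited to the analyses where it can

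*Protocol article*

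**What the plan says.** *Methods for protecting against sources of bias* states that "the trial statistician undertaking the analysis will also be blind to practice allocation". The sentence names no subset of analyses and no point at which the blind is lifted.

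Other parts of the article bear on it:

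- *Setting and clusters*: "Randomisation of GP practices will be undertaken by an independent statistician", and practices are allocated "stratified by the practice size (small or large) in the ratio 1:1". *Evidence of selection bias* confirms that there are "only four clusters randomised".
- *Participant identification and recruitment*, Method 2: "for those GP practices randomised to also offer direct access to physiotherapy, patients who self-refer to physiotherapy will be identified". This route does not operate in control practices, and *Description of intervention and control arms* excludes direct access from control care. The same section says that every patient's pathway is recorded.
- *Explore generalisability of the sample*: "Key characteristics of the participants recruited using each recruitment method will be reported". *Feasibility of study recruitment and retention* also plans counts by recruitment method.
- *Analyses of clinical outcomes*: a comparison of patients referred to physiotherapy in control practices with self-referrers in intervention practices, followed by "We will also compare the self-referrers with those that do not self-refer within the intervention group". The main model in that section has a treatment effect and a random effect for practice.
- *Data confidentiality and archiving*: "The final trial dataset will be accessed by the statistician", together with the principal and chief investigators. No second analyst is listed.

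**The concern.** The article offers blinding of the analyst as a protection against bias, yet some of the analyses it lists cannot be carried out or labelled by someone who does not know the arms. This is a conflict between a stated property and the planned work, which is different from a detail left out.

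What is at stake is mainly accuracy. As worded, a reader would credit the trial with a blind covering all analyses, including those where it is impossible. There is also a practical side. If the fields that reveal allocation reach the statistician before the between-arm models are finished, the blind is lost where it could have been kept.

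**Working it through.** **Step 1. Reproduce the planning figure.** From *Sample size*: 100 consulters per month × 0.80 eligible × 0.50 responding = 40 per practice per month. Over 6 months this is 240 per practice; × 4 practices = 960 at baseline; × 0.80 = 768 followed up. Both stated totals are reproduced. (The 100 per month is the article's rounding of 1250/12 = 104.2.) This point challenges neither figure.

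**Step 2. Sort the planned analyses by whether they need true arm.**

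| Analysis | Needs true arm or pathway? |
|---|---|
| Baseline table by arm | No; a coded arm is enough, and its listed variables include neither pathway nor recruitment method |
| Mixed models for SF-36v2 PCS and secondary outcomes | No; coded arm, practice code, time and the listed patient covariates |
| Referred in control v self-referring in intervention practices | Yes, by definition |
| Self-referrers v others within the intervention group | Yes, by definition |
| Counts and characteristics by recruitment method | They use a field with one category that occurs only in intervention practices |

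The third and fourth rows settle the matter without arithmetic: whoever runs them knows which practices are intervention practices.

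**Step 3. How revealing are the pathway fields?** Allocation in the ratio 1:1 of four practices gives two per arm.

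- With an arm code present, one self-referral record anywhere shows which code is intervention, and so the arm of all four practices.
- With only practice codes present, self-referrers in two different practices identify all four.

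**Step 4. Illustrate with numbers.** Let m be the physiotherapy patients per intervention practice in the research sample and p the share of them by direct access. The article expects 20–25% to be referred to physiotherapy, a figure stated for control practices and assumed here for intervention practices. Then m = 240 × 0.20 to 240 × 0.25 = 48 to 60. The article's minimum target for p is 20%; the lower values are sensitivity checks.

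P(no self-referrer in a practice) = q = (1 − p)^m. P(at least one in both intervention practices) = (1 − q)².

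| p | Expected per practice, m × p | q | (1 − q)² |
|---|---|---|---|
| 20% | 9.6 to 12.0 | 0.000022 to 0.0000015 | above 0.9999 |
| 10% | 4.8 to 6.0 | 0.0064 to 0.0018 | 0.987 to 0.996 |
| 5% | 2.4 to 3.0 | 0.085 to 0.046 | 0.84 to 0.91 |

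With an arm code present, the chance that no self-referrer appears anywhere in the arm is (1 − p)^(2m). At p = 5% this is 0.95^96 = 0.7% to 0.95^120 = 0.2%. So even at a quarter of the target, the chance of revealing the allocation exceeds 99% once pathway and arm code are seen together.

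**The case against.** The strongest reply is that the blind can hold where it matters most. The PCS and secondary-outcome models need only a coded arm and a practice code and use no pathway variable. An independent statistician randomises, so the analyst does not learn the allocation that way. Coded arms, withheld fields and the timing of unblinding normally belong in the statistical analysis plan or the trials unit's procedures, which are not shown; *Trial organisation and monitoring* refers to approval of such a plan. All of this stands, and the lack of a described staging is not itself a fault. It does not rescue the sentence as printed: no analysis plan can make an unlimited claim of blinding true while the arm-defined comparisons are part of the analysis.

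Three stronger readings are tempting, and the document does not support them.

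- A reader might infer that the safeguard does not exist at all. Nothing printed rules out blind fitting of the main models followed by unblinding. The sections on recruitment counts, the direct-access audit and generalisability name no analyst, and the audit uses anonymised data.
- A reader might infer that the feasibility decision is affected, because selection bias is judged by inspecting the baseline table without a numerical rule. That judgement is the team's, and the article does not promise to blind the team. The principal investigator and study team are in regular contact with control practices. The stated criteria of 40% recruitment, 70% retention at 6 months and 20% direct access are proportions that knowledge of arm does not alter.
- A reader might infer that unmasking is practically certain at the first tabulation. The probabilities above apply only once pathway or recruitment method is seen beside an arm or practice code. The article does not say when that happens, nor which fields the final dataset contains.

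**Conclusion.** The point holds in a limited form. The blinding statement cannot apply to the whole analysis described, because two planned comparisons are defined by true arm. Recruitment-method or pathway data seen alongside arm or practice codes would also identify the arm of all four practices. The first part follows from the text alone. The numerical illustration for the second assumes that the 20–25% referral share carries over to intervention practices (its wording may also cover diagnostic tests and other services), equal practice sizes, independent patients, and the same research uptake among self-referrers as among others. The conclusion does not depend closely on these.

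The consequence is modest. Outcomes are self-reported, the main model is specified, the clinical analyses are exploratory and mainly descriptive with no emphasis on p values, and no sample-size or precision figure changes. It is a correction to a stated property, worth making because it is nearly free and secures the blind where it can exist.

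**What to change.** In *Methods for protecting against sources of bias*, limit the claim to the baseline table by arm and the between-arm models for PCS and the secondary outcomes. Run and lock these on coded arms and practice codes, with recruitment method, referral pathway and any other field collected only for direct-access patients withheld from the statistician. Release those fields afterwards for the pathway and recruitment-method analyses, or have a separate, existing team member run those analyses. If neither is wanted, state that the research nurses are blind and the statistician is not.

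The cost is a sentence of wording, a two-step data release by the trials unit and a short delay to the pathway analyses. No change to recruitment, data collection or the models is needed.
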